## Material and method

2

### Study design

2.1

The study protocol is a randomized, controlled, double-blind design. The study protocol was approved through Institutional Review Board in the People's Hospital of Beilun district of Ningbo (HN20201208) and was registered in the OSF Registries (with number: 10.17605/OSF.IO/PZ9ES).

### Participants

2.2

The study included patients with idiopathic adhesive capsulitis of the shoulder between the ages of 18 and 80 years who had primary adhesive capsulitis of the shoulder. Our diagnosis of adhesive capsulitis of the shoulder was based on a consensus definition, characterized by functional restriction of both active and passive shoulder motion for which radiographs of the glenohumeral joint are essentially unremarkable. All patients underwent a thorough history, physical examination, and radiographic imaging studies, including standard plain radiographs and ultrasound imaging scan by the treating orthopedic surgeon with 10-year of shoulder US experience.

The exclusion criteria for the study were patients with diagnosed rotator cuff tear, calcific tendinitis, or impingement syndrome by ultrasound imaging, patients with symptomatic cervical radiculopathy, patients with previous fracture or surgery around shoulder, acute or chronic infection around shoulder, a pregnancy, patients with a recent history of injection around the shoulder (within 6 weeks), and other secondary conditions possibly related to shoulder dysfunction (rheumatologic disease or hemiplegia).

### Recruitment and randomization

2.3

Recruitment will be started in March 2021 and completed in October 2022. The treating surgeon will assess 90 patients for eligibility. Written informed consent will be obtained from patients. Then, each patient will be randomized into 3 treatment groups, receiving PRF stimulation of the SSN or physical therapy or both of them. To allocate treatment, a randomization sequence with random permuted blocks will be generated by randomization program on internet website (www.randomizer.org). Sequentially numbered opaque sealed envelopes containing treatment allocations will be prepared and opened in sequence by an independent research assistant who is not involved in treatment. All the data collectors, surgeons, statistical analysts, as well as result assessors are not aware of grouping assignment (Fig. 1).

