### Intervention protocol

2.4

In order to perform the surgical procedure under strict sterile conditions, the PRF lesioning procedure will be performed in the operating room. Each patient is placed in a prone position, and the skin overlying the operation area is prepared and draped. A standard RF lesion generator (Neurotherm JK 25T) is used for the whole procedure. The suprascapular notch is identified under C-arm fluoroscopy at an angle slightly oblique to the treated side and angled cephalo-caudal. After sterile preparation and administration of local anesthesia, a 22-gauge 10 mm active tip RF needle 10 cm in length is inserted and advanced toward the suprascapular notch. Proper localization of nerve is achieved by sensory and motor stimulation. Sensory stimulation is performed (50 Hz; 1 ms pulsed width; up to 0.5 volt) and the patient reports paresthesia in the shoulder joint. Upon motor stimulation (2 Hz; 1 ms pulsed width; up to 1 V), muscle contractions in the suprascapular and infrascapular muscles are observed. Two PRF cycles of 180 s are performed after localization. The RF current is delivered at a width of 20 ms and at 45 V. The tip temperature works at 38°C initially, and then the temperature increases slowly to 42°C within 30 s. The patients are observed for 30 min after the PRF lesioning procedure. If no significant complications (including pain, bleeding, and pneumothorax) are observed, the patient will be discharged.

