### Physical therapy

2.5

Initially, hot pack application and transcutaneous electronic nerve stimulation are performed for groups. Then, for 12 weeks, stretching exercises, mobilization, and therapeutic exercises (30 min per session, 3 sessions per week) are performed under the guidance of a therapist who is blinded to patient allocation.

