### Outcomes parameters

2.6

All patients will be assessed for pain and functional status before and immediately after the treatment by a researcher blinded to the patient groups. The range of shoulder mobility and functional status will be assessed using the Constant Shoulder Scale, which was developed to evaluate functional recovery of the shoulder. The total Constant score ranges from 0 to 100 points, with higher scores indicative of better function. The score is divided into four sections: pain (15 points), activities of daily living (20 points), range of motion (40 points), and strength (25 points). Pain is scored using a visual analog scale. The activities of daily living score are divided into 4 subscales of sleep, work, recreational activities, and ability to position the hand in space. Range of motion is assessed in 4 active positions, with 10 points for each. Flexion and abduction are assessed by a goniometer, whereas functional internal and external rotation is assessed by the position of the hand. Strength is tested by a calibrated spring dynamometer, at 90° abduction of the shoulder with the forearm pronated and scored as the maximum of 3 repetitions (Tables 1 and 2).

**Table 1 T1:** Patient baseline demographics.

Demographics	Combined group	PRF lesioning of the SNN group	Ultrasound group	*P*
Number of patients (shoulders)				
Age, yr				
Male sex [no. (%)]				
BMI^∗^, kg/m^2^				
Left side [no. (%)]				
Follow-up^∗^				

BMI = body mass index, PRF = pulsed radiofrequency, SSN = suprascapular nerve.

∗ The values are given as the mean and the SD.

**Table 2 T2:** Postoperative outcomes.

Outcomes	Combined group	PRF lesioning of the SNN group	Ultrasound group	*P*
VAS				
Constant score				
Range of motion				
Muscle strength				

PRF = pulsed radiofrequency, SSN = suprascapular nerve, VAS = visual analog scale. The values are given as the mean and the SD.

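### The double-blind label and the claims of surgeon and therapist blinding conflict with three visibly different arms and no described sham; pain is rated by unblinded patients, though assessors and analysts can be blind

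*Protocol article*

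**What the plan says.** Section 2.1 states: "The study protocol is a randomized, controlled, double-blind design". The same label appears in the Abstract (Background and Methods), the Introduction and the Discussion.

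Section 2.3, like the Abstract, lists who is masked: "All the data collectors, surgeons, statistical analysts, as well as result assessors are not aware of grouping assignment". Patients are not on that list. Section 2.5 adds that the exercise course is given "under the guidance of a therapist who is blinded to patient allocation".

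Section 2.3 defines the arms as patients "receiving PRF stimulation of the SSN or physical therapy or both of them". Section 2.4 says that "the PRF lesioning procedure will be performed in the operating room", under local anesthesia. During nerve localization "the patient reports paresthesia in the shoulder joint" and "muscle contractions in the suprascapular and infrascapular muscles are observed". Section 2.5 describes 12 weeks of guided exercise, three 30-minute sessions a week.

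On outcomes, section 2.6 says a researcher blinded to the groups assesses patients, and "Pain is scored using a visual analog scale". Section 2.7 sizes the trial on the pain score (3 cm difference, SD 3.49).

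**The concern.** The label, the word surgeons in the masked list and the unqualified therapist claim all assert a protection against bias. The arm definitions and procedures in the same article do not allow that protection. A patient who has had a needle procedure in an operating room, a 12-week exercise course, or both can tell which it was.

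This matters most for pain, because the patient supplies the rating. A blinded researcher who records that rating does not blind it. Expectation would plausibly favour the arm that receives both treatments, which is the direction of the trial's hypothesis. If the label stands, the trial report will carry it forward, and readers will give the pain result more credit than the design supports.

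**Working it through.** **1. Each role against the procedures.** The arms are PRF only, therapy only, and both. No sham PRF or sham therapy is described, and an arm defined as one treatment alone leaves no room for one.

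| Role | What the article claims | What sections 2.3 to 2.5 allow |
|---|---|---|
| Patient | Implied by the label; not on the masked list | Knows which treatments were received; is alert enough during PRF to report paresthesia |
| PRF operator | Surgeons unaware | Knows the patient is not in the therapy-only arm; can be unaware whether therapy is also assigned |
| Therapist | Blinded, without qualification | Knows the patient is not in the PRF-only arm; can be unaware whether PRF was given |
| Data collector, assessor, analyst | Unaware | Can be blind |

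Section 2.5 says that hot packs and nerve stimulation are given for groups, without saying which. Even if all arms received them, they would mask neither the PRF procedure nor the exercise course.

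**2. Which outcomes are exposed.** VAS pain is self-report. In the Constant score, pain (15) + daily living (20) = 35 of 100 points are self-reported. Range of motion (40) + strength (25) = 65 points are measured. Range of motion is taken in active positions and strength is the best of three repetitions, so both depend on the effort of an unblinded patient.

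**3. Pain is the sizing variable.** Inputs from section 2.7: difference 3 cm, SD 3.49, alpha 0.05, power 0.80, stated n = 25. Sidedness, and whether 25 is per group, are not stated; I take two-sided and per group.

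- Normal formula: n = 2 × (1.96 + 0.84)² × 3.49² / 3² ≈ 21.2, so 22 per group.
- t-test: 22.25, so 23 per group.
- t-test n divided by 0.864 (minimum efficiency of the rank test): 25.7, so 26 per group.

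The stated 25 is thus approximately recovered as a per-group figure for a two-group comparison of pain. The patient-rated VAS is the outcome on which the trial's size rests.

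**4. Illustration of what unblinded rating could do.** The documents give no expectation effect. I assume no true difference, equal allocation (90 / 3 = 30 per arm), SD 3.49, normal data, and a spurious shift of 0.5 or 1.0 cm in the combined arm only. That is 0.5/3 = 17% and 1.0/3 = 33% of the 3 cm target.

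For a pairwise t-test, the standard error of a difference is 3.49 × √(2/30) = 0.901. The shift divided by the standard error is 0.555 or 1.110. For the planned three-group Kruskal-Wallis test, the rates come from simulation.

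| Assumed shift | Kruskal-Wallis, three groups | Pairwise t-test |
|---|---|---|
| 0 cm | about 5% | 5.0% |
| 0.5 cm | about 7.7% | 8.5% |
| 1.0 cm | about 17.6% | 19.4% |

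The Kruskal-Wallis column is the relevant one, because section 2.7 names that test for the between-group comparison and names no pairwise test.

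**The case against.** The strongest case on the other side has four parts.

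*Much of the stated blinding is feasible.* A reader might infer that the stated blinding does not exist at all. The article does not support that. Of the four roles listed in section 2.3, data collectors, analysts and assessors can be masked, and section 2.6 separately assigns assessment to a blinded researcher. An independent assistant opens the envelopes, so surgeon and therapist can each be unaware of the other component. This stands, and it limits the point to patients and to staff for the component they deliver.

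*An article condenses the full protocol.* This would answer a missing detail. Here the article makes positive statements that its own sections 2.3 to 2.5 contradict. If a sham exists in the full protocol, the arm definitions in 2.3 are what need correcting, so a change is needed either way.

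*The magnitude is assumed.* This stands. The shift is not taken from the documents, and a wording change would not reduce it. A reader might take the 8% to 18% as the trial's actual error rate; it is illustration only.

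*Range of motion and strength offer a blinded check.* Only in part. The assessor is blind, but the patient is not, and both measures depend on effort. Calling those results blinded without qualification would repeat the same overstatement.

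**Conclusion.** The point holds in a limited form. The double-blind label, the claim that surgeons are unaware of assignment and the unqualified therapist claim are wrong as written. Patients know what they received, and operator and therapist can each exclude one of the three arms. Assessor, data-collector and analyst blinding is compatible with the design.

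The consequence falls on VAS pain, the outcome that sizes the trial, and on 35 of the 100 Constant points, all rated by unblinded patients. This conclusion rests only on the text and on no sham being described. The illustrative rise from about 5% to about 8% to 18% rests further on the assumed shift of 0.5 to 1.0 cm, equal allocation and normal data. The contradiction stands without it.

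**What to change.** 1. In the Abstract, Introduction, section 2.1 and Discussion, replace the double-blind label with: assessor- and analyst-blinded; patients and treating staff not blinded to the treatment given or received.
2. In the Abstract and section 2.3, limit the surgeon claim to being unaware of whether physical therapy is also assigned. In section 2.5, limit the therapist claim to being unaware of whether PRF was given. Alternatively, remove both claims.
3. Interpret VAS pain and the self-reported Constant items as unblinded self-report. Read them alongside range of motion and strength, described as assessor-blinded but effort-dependent.
4. If the full protocol does contain a sham, correct the arm definitions in section 2.3 instead.

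The change is wording only; sample size, visits and treatments are untouched. The downside is a less favourable blinding label. It corrects the stated protection and the conclusions drawn from it, but it does not remove any expectation bias.

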**Figure 1 F1:**
[figure not shown]
Consolidated Standards of Reporting Trials (CONSORT) diagram of patient flow through the study.

### Intervention protocol

2.4

In order to perform the surgical procedure under strict sterile conditions, the PRF lesioning procedure will be performed in the operating room. Each patient is placed in a prone position, and the skin overlying the operation area is prepared and draped. A standard RF lesion generator (Neurotherm JK 25T) is used for the whole procedure. The suprascapular notch is identified under C-arm fluoroscopy at an angle slightly oblique to the treated side and angled cephalo-caudal. After sterile preparation and administration of local anesthesia, a 22-gauge 10 mm active tip RF needle 10 cm in length is inserted and advanced toward the suprascapular notch. Proper localization of nerve is achieved by sensory and motor stimulation. Sensory stimulation is performed (50 Hz; 1 ms pulsed width; up to 0.5 volt) and the patient reports paresthesia in the shoulder joint. Upon motor stimulation (2 Hz; 1 ms pulsed width; up to 1 V), muscle contractions in the suprascapular and infrascapular muscles are observed. Two PRF cycles of 180 s are performed after localization. The RF current is delivered at a width of 20 ms and at 45 V. The tip temperature works at 38°C initially, and then the temperature increases slowly to 42°C within 30 s. The patients are observed for 30 min after the PRF lesioning procedure. If no significant complications (including pain, bleeding, and pneumothorax) are observed, the patient will be discharged.

### Physical therapy

2.5

Initially, hot pack application and transcutaneous electronic nerve stimulation are performed for groups. Then, for 12 weeks, stretching exercises, mobilization, and therapeutic exercises (30 min per session, 3 sessions per week) are performed under the guidance of a therapist who is blinded to patient allocation.

### Outcomes parameters

2.6

All patients will be assessed for pain and functional status before and immediately after the treatment by a researcher blinded to the patient groups. The range of shoulder mobility and functional status will be assessed using the Constant Shoulder Scale, which was developed to evaluate functional recovery of the shoulder. The total Constant score ranges from 0 to 100 points, with higher scores indicative of better function. The score is divided into four sections: pain (15 points), activities of daily living (20 points), range of motion (40 points), and strength (25 points). Pain is scored using a visual analog scale. The activities of daily living score are divided into 4 subscales of sleep, work, recreational activities, and ability to position the hand in space. Range of motion is assessed in 4 active positions, with 10 points for each. Flexion and abduction are assessed by a goniometer, whereas functional internal and external rotation is assessed by the position of the hand. Strength is tested by a calibrated spring dynamometer, at 90° abduction of the shoulder with the forearm pronated and scored as the maximum of 3 repetitions (Tables 1 and 2).

**Table 1 T1:** Patient baseline demographics.

Demographics	Combined group	PRF lesioning of the SNN group	Ultrasound group	*P*
Number of patients (shoulders)				
Age, yr				
Male sex [no. (%)]				
BMI^∗^, kg/m^2^				
Left side [no. (%)]				
Follow-up^∗^				

BMI = body mass index, PRF = pulsed radiofrequency, SSN = suprascapular nerve.

∗ The values are given as the mean and the SD.

**Table 2 T2:** Postoperative outcomes.

Outcomes	Combined group	PRF lesioning of the SNN group	Ultrasound group	*P*
VAS				
Constant score				
Range of motion				
Muscle strength				

PRF = pulsed radiofrequency, SSN = suprascapular nerve, VAS = visual analog scale. The values are given as the mean and the SD.

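### The only post-baseline assessment is tied to the end of each patient's treatment, so read literally PRF alone is scored about 12 weeks before the other two arms

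*Protocol article*

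**What the plan says.** Section 2.3 defines the arms: "each patient will be randomized into 3 treatment groups, receiving PRF stimulation of the SSN or physical therapy or both of them".

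Section 2.4 describes PRF as one procedure. "Two PRF cycles of 180 s are performed after localization", and then "The patients are observed for 30 min after the PRF lesioning procedure", with discharge if no significant complication is seen.

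Section 2.5 starts physical therapy with hot packs and nerve stimulation, for a period it does not state. It continues: "Then, for 12 weeks, stretching exercises, mobilization, and therapeutic exercises (30 min per session, 3 sessions per week) are performed".

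Section 2.6 gives one assessment rule for everyone: "All patients will be assessed for pain and functional status before and immediately after the treatment". It names no week, window or reference to randomisation.

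Section 2.7 compares baseline with a post-treatment score inside each group by the Wilcoxon signed-rank test, and compares the groups by Kruskal-Wallis. Neither analysis has a time term. The shell of Table 1 has a Follow-up row, to be given as mean and SD, with no defined length. The title of Table 2 calls the outcomes postoperative, although the physical-therapy-alone arm has no operation.

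**The concern.** The stated aim is the synergistic effect of PRF plus physical therapy, so the combination has to be compared with each component. If the outcome is taken when each patient's own treatment ends, and one treatment lasts minutes while the other lasts at least 12 weeks, the arms are measured at different points in the course of the disease. Any change over those weeks that has nothing to do with treatment, such as natural course or regression to the mean, then enters the difference between arms.

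This is a timing rule that the article states, and not a detail left to an analysis plan. If the PRF-alone arm has no later measurement, no analysis can supply one.

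**Working it through.** **Step 1. When each arm is scored under the literal rule.** The times below are inferred from the stated durations. The article does not give them as calendar times.

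| Arm | End of own treatment | Approximate score time |
|---|---|---|
| PRF alone | two 180 s cycles, 30 min observation (2.4) | procedure day |
| Physical therapy alone | initial phase, then 12 weeks (2.5) | week 12 or later |
| Combined | as physical therapy; the Introduction places PRF before it | week 12 or later |

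The gap between PRF alone and the other two arms is at least 12 × 7 = 84 days. It enters two of the three pairwise contrasts and the omnibus test. Combined and physical therapy alone are scored at about the same stage.

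**Step 2. Does another reading give a common time?**

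- If the phrase means after PRF for everyone, the combined arm is scored before its therapy and the therapy-alone arm has no reference point.
- If it means the end of the trial's treatment period, the three arms would line up, but the article does not say so.
- The Follow-up row in Table 1 is blank and undefined, so it does not settle the matter.

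**Step 3. The plan's own figure.** Section 2.7 uses a difference of 3 cm, SD 3.49, alpha 0.05 and power 0.8, and states a sample size of 25, read here as per group.

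- Normal approximation: 2 × (1.960 + 0.842)² × (3.49/3)² = 21.2, so 22.
- Two-sample t-test: 22.25, so 23.
- t-test value adjusted for a rank test: 22.25/0.955 = 23.3, so 24.

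The stated 25 is within two of the t-test and rank-test results. The timing point does not depend on it and does not change it.

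**Step 4. Illustration of size.** Inputs from the article are SD 3.49, 90 patients and significance at 0.05. Assumptions are equal allocation (90/3 = 30 per arm), a two-sided test, normal data, no treatment difference at any common time, and a shift in both therapy arms that is due only to elapsed time. The article gives no figure for that shift, so a range is shown.

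For combined versus PRF alone, the standard error is 3.49 × √(2/30) = 0.901 cm. The noncentrality is shift/0.901, and the critical value is 2.002 on 58 degrees of freedom. The Kruskal-Wallis column was simulated with 6,000 trials per row, so its standard error is at most √(0.25/6000) = 0.65 percentage points.

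| Assumed shift (cm) | Noncentrality | False-positive rate, t-test | False-positive rate, three-group Kruskal-Wallis |
|---|---|---|---|
| 0 | 0 | 5% | about 5% |
| 0.5 | 0.55 | 8.5% | about 7% |
| 1 | 1.11 | 19.4% | about 18% |
| 1.5 | 1.66 | 37.4% | about 35% |
| 2 | 2.22 | 58.8% | about 58% |

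Section 2.7 names Kruskal-Wallis and no pairwise test, so the last column is closest to the written analysis. The two columns lead to the same conclusion.

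**The case against.** The best reply is that the procedure-day assessment is an inference. One rule for all patients could mean the end of the trial's treatment period. The instrument favours that reading, because the Constant score includes sleep, work and recreation, which can hardly be scored minutes after a procedure. A Follow-up row also hints at later contact, and a condensed article may omit a visit schedule. This stands as far as it goes: the intended schedule may be sound. But the article states a rule, that rule gives unequal times when applied as written, and nothing in the article corrects it.

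A reader might infer more than the text supports:

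- **That every treatment comparison is confounded.** Combined versus physical therapy alone is measured after the same course in both arms. It isolates the addition of PRF, which is the rationale in the Introduction and Discussion.
- **That local anaesthesia distorts the PRF-alone scores.** Section 2.4 says "After sterile preparation and administration of local anesthesia" but gives no agent, amount or duration. It then expects the patient to report paresthesia and expects muscle contractions on stimulation. An effect on scores is conjecture, and on pain it would favour PRF alone.
- **That the bias must favour the combination.** Improvement over time would push that way, but other influences could oppose it.
- **That the Discussion predicts drop-out here.** It reports patients in previous studies who could not finish rehabilitation. It makes no forecast for this trial.
- **That a mean and SD for follow-up proves no common visit exists.** Actual follow-up varies around fixed visits too.

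**Conclusion.** The concern holds within limits. The assessment rule in section 2.6, combined with the treatment durations in sections 2.4 and 2.5, confounds treatment with elapsed time in PRF alone versus combined, in PRF alone versus physical therapy, and in the three-group test. The remaining contrast is largely free of the problem.

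This rests on reading the rule literally. The rates in the working show only how quickly a modest time effect would raise the error rate. They are not estimates of what will happen in this trial, because the shift is assumed and its true size and net direction cannot be derived from the documents. The need for correction does not depend on the size of the shift, since a missing later measurement for PRF alone could not be recovered at analysis.

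**What to change.** In section 2.6, replace the post-treatment rule with one primary assessment time that:

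- is counted from randomisation and is identical in all three arms;
- falls at or after the planned end of the whole therapy course, meaning the initial phase plus the 12 weeks, and has a stated window;
- applies to every randomised patient, whether or not treatment was completed.

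A visit at exactly 12 weeks from randomisation could fall before therapy ends, because section 2.5 puts a phase of unstated length before the 12 weeks. The length of that phase should therefore be stated when the time is chosen. The choice of week is the sponsor's.

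Treat any same-day score after PRF as descriptive, and retitle Table 2 to the chosen time point.

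The cost is a short protocol change and one later outcome visit for the PRF-alone arm. The sample size is unchanged.
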